# Figure-of-eight bandage versus arm sling for treating middle-third clavicle fractures in adults: study protocol for a randomised controlled trial

**DOI:** 10.1186/s13063-016-1355-8

**Published:** 2016-05-04

**Keywords:** Clavicle, Fracture healing, Fractures, Bone, Treatment outcome, Pseudarthrosis, Conservative treatment

## Abstract

**Background:**

Fracture of the clavicle is common, accounting for 2.6 to 4.0 % of all fractures, with an overall incidence of 36.5 to 64 per 100,000 per year. Around 80 % of clavicle fractures occur in the middle third of the clavicle. Randomised controlled trials comparing treatment interventions have failed to indicate the best therapeutic practices for these fractures. The objective of this study is to evaluate the effects (benefits and harms) of two commonly-used conservative interventions: the figure-of-eight bandage versus the arm sling as treatments of middle-third clavicle fractures.

**Methods/design:**

This project has been designed as a single-centre, two-arm randomised controlled trial that will compare two interventions: figure-of-eight bandage versus the arm sling. We propose to recruit 110 adults, aged 18 years or older, with an acute (less than 10 days since injury) middle-third clavicle fracture. The primary outcomes to be evaluated will be function and/or disability measured by the Disability of the Arm, Shoulder, and Hand (DASH) questionnaire. In order to assess the secondary outcomes, the Modified University of California at Los Angeles (modified – UCLA) Shoulder Rating Scale will be used. The occurrence of pain (Visual Analogue Scale for pain (VAS)), treatment failure, adverse events and the ability to return to previous activities will also be recorded and evaluated as secondary outcomes. Data analysis*:* the primary outcome DASH score and the secondary outcomes – modified UCLA and VAS scores – will be analysed graphically. We will apply generalised mixed models with the intervention groups (two levels), and time-point assessments (seven levels) as fixed effects and patients as a random effect.

**Discussion:**

According to the current literature there is very limited evidence from two small trials regarding the effectiveness of different methods of conservative interventions for treating clavicle fractures. This is the first randomised controlled trial comparing the figure-of-eight bandage versus the arm sling for treating clavicle fractures that follows the CONSORT Statement guidelines.

**Trial registration:**

ClinicalTrials.gov NCT02398006.

**Electronic supplementary material:**

The online version of this article (doi:10.1186/s13063-016-1355-8) contains supplementary material, which is available to authorized users.

## Background

Fracture of the clavicle accounts for 2.6 to 4 % of all fractures, with an overall incidence of 36.5 to 64 per 100,000 per year [1–3]. The incidence is bimodal with peak incidence in youth and in later life with a male excess in the young and a female excess (7:1) in later life [1]. The most common site of fracture is the middle third of the clavicle, representing approximately 80 % of all clavicle fractures [3, 4].

Traditionally, middle-third clavicle fractures have been treated conservatively, even when substantially displaced [5, 6]. A large number of methods to immobilise the region have been described. However, the most common methods are the use of a figure-of-eight strap (Fig. 1a), an arm sling (Fig. 1b), or a combination of the two [4, 7–9]. Indications for surgery include open fractures, severe displacement caused by comminution, suspicion of imminent skin lesion production by a sharp clavicle fracture edge, or neurovascular injuries. Relative indications for surgery include polytrauma, floating shoulder, painful malunion and painful nonunion. More recently though, the scope of indications has widened to include high-energy fractures, such as clavicle shortening of greater than 20 mm, complete displacement and severe comminution. There are several fixation techniques that can be used [10–13]. The most frequently used is internal fixation with plates or wires. Bone grafting may also be used [4, 9, 14, 15].

**Fig. 1 Fig1:**
[figure not shown]
Conservative management to clavicle fractures: **a** Figure-of-eight bandage. **b** Simple arm sling

In contrast to fractures at other skeletal sites, there are only few randomised trials which have compared either conservative or surgical approaches to the management of clavicle fracture. In addition, the available evidence from isolated trials is limited regarding the effectiveness of the different methods of surgical and conservative interventions [16–18].

Lenza et al. [16] concluded that evidence of only two clinical trials published in the 1980s [7, 19] is insufficient to determine the effects (benefits and harms) of the different methods of conservative (non-operative) treatments for acute (treated soon after diagnosis) middle-third clavicle fractures in adults. A search strategy, updated in January 2014, did not find any new comparative studies on conservative interventions for treating clavicle fractures.

Current literature reinforces the view that the best conservative treatment for middle-third clavicle fractures in adults is controversial. A recent survey indicates that most US surgeons prefer to use a simple sling rather than the figure-of-eight bandage for conservatively treating their patients (94 % prefer the simple sling versus 6 % prefer the figure-of-eight bandage) [20]. In contrast, a survey on conservative treatment of clavicle fractures in Germany concluded that the simple clavicle fractures are treated in a nonsurgical way and orthopaedic surgeons prefer the use of the figure-of-eight bandage in 88 % of cases [21].

Therefore, there is a need to investigate which would be the best intervention (considering functional endpoints and adverse effects) in patients with clavicle fractures. Since nonsurgical treatments are the most prevalent in current clinical practice, the authors of this study chose to evaluate the effects (benefits and harms) of conservative interventions: the figure-of-eight bandage versus the arm sling, for treating middle-third clavicle fractures.

## Methods/design

This project has been designed as a single-centre, two-arm (parallel) randomised controlled trial with follow-up at 12 months, following the Consolidated Standards of Reporting Trials (CONSORT) Statement [22–25] (Fig. 2 shows the participant flow diagram). This study will be carried out at Hospital Municipal [name] in São Paulo, Brazil (a medium-complexity, public tertiary hospital), between May 2015 and March 2017. This study was approved by the ethical committee (CEP Hospital Israelita Albert Einstein/Plataforma Brasil 1966-14) and was registered in the ClinicalTrials.gov database (NCT02398006).

**Fig. 2 Fig2:**
[figure not shown]
Flow of participants. Diagram shows the planned flow of participants through each stage of the study

The trial will last a total of 26 months. The initial 2 months will be a pre-trial period to be followed by a recruitment period of 10 months. The subsequent 12 months will cover the treatment and follow-up periods (these will overlap the recruitment phase) and a final 2 month period will be dedicated to data analysis.

### Participants

To be eligible, participants must meet the following criteria:

Inclusion criteria:Adults aged between 18 and 65 years with a middle-third clavicle fractureAcute fracture (less than 10 days), comprising all types of middle-third clavicle fractures (non-displaced and displaced fractures)No medical contraindication to proposed methods of immobilisationUnderstanding of the Portuguese language and providing written informed consent

Exclusion criteria:Pathological fractureOpen fractureNeurovascular injury on physical examinationAssociated head injury (Glasgow Coma Scale score <12)Ipsilateral upper limb fractures and/or dislocation (except of the hand and fingers)History of frozen shoulderPrevious disease in the limb that could influence the results (e.g. rheumatoid arthritis)Inability to comply with follow-up (inability to read or complete forms)

### Interventions

Group 1: the orthopaedic surgeon will apply a figure-of-eight bandage (UDINE®) (Fig. 1a) – no attempt will be made to reduce the fracture. The figure-of-eight bandage will be used for 4 weeks, and every week the participants will return for checking and adjusting the immobilisations. In this way, the dominant arm can remain free and simple activities will be allowed (writing, keyboarding and other). Participants and relatives of participants will also be educated on how to tighten the bandage when necessary. The figure-of-eight bandage should be adjusted so that the shoulder is pressed back in an arched position, almost like a back-stretch.

The figure-of-eight should be used all day (including bath-time and bed-time); participants will be instructed not to remove the immobilisations. Patients will be instructed on how to properly wear and adjust the immobilisations should they slacken or be removed from the shoulders. The following fitting instructions will be given:Place arms through arm straps so that the felt pad is located on the back and the foam insert is placed between the shoulder bladesAdjust by pulling the arm straps tight. Fasten the contact closures on the arm padThe cushioned arm pad should be adjusted so that it fits under the arm and in front of the shoulder. The straps should be tight enough to pull the shoulders back

A sponge bath or a tub bath will be recommended. Patients will also be advised that during the night a rolled up towel can be placed on the bed between their shoulder blades. This helps to keep the shoulder in the correct position while asleep.

After 4 weeks, participants will be encouraged to discard the bandage. Load bearing will not be allowed before osseous consolidation (around 10 weeks).

Group 2: the orthopaedic surgeon will apply a standard arm sling (UDINE®) (Fig. 1b) that will be used for 4 weeks. The upper limb will be immobilised in internal rotation. The arm sling goes from the elbow of the injured arm, across the back to the patient’s opposite shoulder. The patient’s hand should be at or above the level of his/her elbow. Participants will be instructed to flex and extend their elbows for 10 minutes, three times a day. The patient will be allowed to remove the sling during bath-time. Load bearing will only be allowed after 10 weeks following the intervention.

All participants (of the two groups) will be placed on the standard analgesia protocol at our institution, which consists of patient-controlled ingested paracetamol (3 g/day) and/or sodium diclofenac (150 mg/day). On the final day of analgesic treatment (7 days), the total consumption of each drug will be recorded.

#### Care programme

Identical rehabilitation will be carried out in both intervention groups. After 4 weeks of treatment, a senior physiotherapist will instruct the participants on some simple standard home stretching exercises, which should be done daily for 30 minutes per day; these will be forward elevation and external rotation stretches and Codman pendulum exercises [26].

#### Assessment

After signing the consent form (Additional files 1 and 2), the researchers will collect the demographic data from all patients using a pre-prepared form (Additional file 3). Baseline data collected will include: age, gender, weight, height, addictions (e.g. smoking or alcohol), clinical comorbidities, occupation and mechanism of trauma. All fractures will be classified using the Edinburgh classification proposed by Robinson et al. [27].

### Outcomes

#### Primary outcomes

Function or disability will be measured by the Disability of the Arm, Shoulder, and Hand questionnaire (DASH) [28] using the validated Brazilian Portuguese version [29]. The final score of the DASH questionnaire will be converted to a percentage via the following formula:$$ \mathrm{Scoring}\kern0.5em =\kern0.5em \left[\mathrm{Sum}\kern0.5em \mathrm{of}\kern0.5em \mathrm{answers}\kern0.5em n/n-1\right]\kern0.5em \times \kern0.5em 25, $$

where *n* is the number of complete answers. At least 27 of the 30 items must be completed for a score to be calculated. The value is then transformed to a score out of 100. A higher score indicates greater disability. The two optional modules (sport/music or work) will not be measured.

#### Secondary outcomes

Modified University of California at Los Angeles (modified - UCLA) [30, 31], validated and translated into Portuguese in Brazil [32]Pain measured on a 0 to 100 Visual Analogue Scale (VAS) (with 0 indicating no pain and 100 indicating maximum pain) [33, 34]. As reported in the literature, a clinically important change will be considered as a 30 % or more change in pain score [35, 36]. The total of analgesic consumed by the patients during the follow-up will be analysedTreatment failure will be considered as outcome in those participants who will need (or are being considered for) a surgical intervention (e.g. symptomatic nonunion or malunion with intractable pain). Although studies evaluating patients with fractures without displacement reported low rates of nonunion (about 0.03 %) [5, 6, 15], studies involving patients with displaced fractures found nonunion rates of up to 15 % [37–39]. Therefore, we expect that between 5 % and 10 % of our participants might exhibit symptomatic nonunion during follow-up period. The patients who experience this complication during follow-up will be treated surgically with open reduction and internal fixation with a pre-contoured locking plate placed on the superior surface of the clavicle, and bone grafting when necessaryAdverse events and effects will be evaluated by the following parameters: (a) cosmetic results: perception of deformity or asymmetry (dichotomous data); (b) asymptomatic nonunion (i.e. the fracture has not radiographically healed, although pain is absent); (c) stiffness/restriction of the shoulder movement (compared with contralateral side). We will also address any possible adverse event reported by participants.In 1986, the American Food and Drug Administration (FDA) defined nonunion to be ‘established when a minimum of 9 months has elapsed since injury and the fracture shows no visible progressive signs of healing for 3 months’. However, these criteria cannot be applied to every fracture [37]. Even though nonunion of the clavicle has not been definitively defined in the literature so far, many investigators agree that a diagnosis can be made if consolidation does not happen within 6 months after the injury [38–40]. The verification of the nonunion is made when there is clinical or radiographic evidence showing that healing has ceased and that union is highly improbable. We shall apply 6 months as the criterionNumbers returning to previous activities (work, sport, activities of daily living), including time to return

Following enrolment in the study, the participants will be seen by one author ([name]) at 1, 2 and 4 weeks and 3, 6 and 12 months. All primary and secondary outcomes will be recorded at each time period. Radiographs will be taken until there is evidence of clinical union at 3, 6 and 12 months.

The treatment failures and adverse events will be considered according to their date of occurrence. We will extract adverse event outcome data at the following time periods: short-term follow-up (up to 6 weeks following treatment); intermediate follow-up (more than 6 weeks and up to 6 months after the end of treatment) and long-term follow-up (more than 6 months after the end of treatment).

### Assignment of interventions

All patients will be assessed in the Emergency Room of the Municipal Hospital [name], referral hospital for trauma, and will undergo clinical and radiographic examination with anteroposterior radiographs and a cephalic tilt of 20° (Zanca inclination [41]).

### Data collection and analysis

#### Sample size

Sample size estimations were performed before patient recruitment. The main variable used was the DASH questionnaire. Type I error was pre-established as 5 % (95 % confidence interval) and type II error as 10 % (power of 90 %) with a population standard deviation of 15 %.

In order to calculate our sample size, we used the mathematical method described in the formula below:$$ \mathrm{n}=\left[{\left(\mathrm{Z}\upalpha /2+\mathrm{Z}\upbeta \right)}^2\times {\upsigma}^2\right]/{\upvarepsilon}^2, $$

where Z*α*/2 is the critical value *α* from the standard normal distribution with upper tail; Z*β* is the critical value *β* from the standard normal distribution; *σ* is population standard deviation; *ε* is the difference in the DASH questionnaire, which was assumed to be clinically relevant (10 points = minimal clinically important difference) [28, 42].

Thus, assuming the values described in the text, we have anticipated that 50 participants would be required in each group. Allowing for approximately 10 % loss to follow-up at 12 months, we aim to recruit a total of 110 patients.

#### Data analysis

Demographic and baseline data will be summarised in the two study groups presenting number in each category and percentages of the number of patients in each group for categorical variables and presenting means and standard deviations or medians and quartiles for continuous variables. If we observe some clinically important imbalance between groups regarding to baseline variables we will adjust for them in the main analysis.

Patients, who for any reason may require additional interventions as part of their treatment, will be followed up, and their results will be included in the group into which they had initially been randomised, according to the intention-to-treat principle.

The primary outcome (DASH score) and the secondary outcomes (modified UCLA and VAS scores) will be analysed graphically. We will apply generalised mixed models in the intervention groups (two levels) and time-point assessments (seven levels) as fixed effects. To evaluate the effect of surgical interventions required due to treatment failure in the DASH score a similar model will be adjusted including the effect of surgery (two levels). In this analysis, patients who are undergoing surgery will have the data analysed up to the last assessment before surgery.

Secondary outcomes: treatment failure, adverse events and return to activities will be analysed individually by the chi-square test. The time to return to previous activities will be analysed by a Kaplan-Meier curve and Cox proportional hazard regression. The total analgesic amount consumed by the patients during the follow-up will be analysed by comparing study groups using the Mann-Whitney test.

To handle the effects of missing data we will describe patterns of missingness in the study groups and use the model-based method of multiple imputation to replace missing data.

The significance level of 5 % will be adopted in the analysis of the primary outcome and 1 % in the secondary outcomes, to avoid chance of statistical significance due to multiple tests.

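### Covariates enter the main DASH analysis only if a baseline imbalance is seen, so the primary model is chosen from the data and most of the available precision gain is given up

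*Protocol article*

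**What the plan says.** The planned primary model has treatment group and time as its only fixed effects: "We will apply generalised mixed models in the intervention groups (two levels) and time-point assessments (seven levels) as fixed effects". The abstract adds a random patient effect. Covariates come in by one route, given in the same section: "If we observe some clinically important imbalance between groups regarding to baseline variables we will adjust for them in the main analysis". No variable, size of imbalance or decision-maker is named, and no other section fixes a covariate set.

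The Assessment section shows what will be on file: "Baseline data collected will include: age, gender, weight, height, addictions (e.g. smoking or alcohol), clinical comorbidities, occupation and mechanism of trauma". It adds: "All fractures will be classified using the Edinburgh classification". The inclusion criteria admit every grade of displacement, "comprising all types of middle-third clavicle fractures (non-displaced and displaced fractures"). The section on randomisation mentions no stratification factor. Under Secondary outcomes the protocol cites nonunion of about 0.03% without displacement and up to 15% with it. The Blinding section keeps the statisticians unaware of treatment status until the analyses are finished.

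**The concern.** The sentence is a positive rule for the main analysis. It is not a detail left open for an analysis plan, and a plan that followed it would carry the same weakness. There are two consequences.

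First, whether any covariate enters, and which one, is decided after baseline differences between the groups are seen. The primary model is therefore not fixed in advance.

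Second, a prognostic covariate improves precision in every trial, including those where the groups happen to be balanced. Using it only when imbalance is noticed gives up most of that gain. A test that switches models in this way also no longer has exactly its nominal error rate.

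**Working it through.** **Inputs from the Sample size section.** Two-sided α 5%, power 90%, SD 15, difference 10 DASH points, 50 per group, 110 in total.

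**The plan's own figure.** For two means, n = 2(1.960 + 1.282)² × 15² / 10² = 2 × 23.64 = 47.3, so 48 per group (49 with the t distribution). This agrees with the stated 50. The formula as printed lacks the factor 2 and would give 24, but the stated number is sound.

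**Always adjusting, by formula.** Power = Φ(δ / (15√(1 − R²) × √(2/50)) − 1.96). At δ = 10:
- R² = 0: 10 / (15.00 × 0.2) − 1.96 = 1.37, power 91.5%
- R² = 0.1: 10 / (14.23 × 0.2) − 1.96 = 1.55, power 94.0%
- R² = 0.2: 10 / (13.42 × 0.2) − 1.96 = 1.77, power 96.1%
- R² = 0.3: 10 / (12.55 × 0.2) − 1.96 = 2.02, power 97.9%

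**The stated rule, by simulation.** Assumptions not in the documents: half the fractures displaced, displacement the only covariate, adjustment triggered when the displaced share differs by 15 percentage points or more, and R² from 0 to 0.3. There were 40,000 trials per cell (80,000 under the null), 50 per arm, one time point and t tests. The trigger fires in about 13% of trials. The second column is the mean DASH difference between displaced and non-displaced fractures that each R² implies: 2 × 15 × √R².

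| R² | Implied difference | Type I error, rule | Power at 10 points: rule / always | Power at 7.5 points: rule / always |
|---|---|---|---|---|
| 0 | 0 | 5.0% | 91 / 91% | 70 / 69% |
| 0.02 | 4.2 | 4.9% | 91 / 91% | 69 / 70% |
| 0.05 | 6.7 | 4.8% | 91 / 92% | 70 / 72% |
| 0.1 | 9.5 | 4.5% | 91.5 / 93% | 70 / 74% |
| 0.2 | 13.4 | 4.1% | 92 / 95.5% | 71 / 79% |
| 0.3 | 16.4 | 3.6–3.8% | 93 / 97.5% | 72.5 / 84% |

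Always adjusting holds about 5% type I error throughout, and no adjustment gives about 91% power at 10 points. At R² = 0.3, always adjusting gains 97.5 − 91 = 6.5 points and the rule gains 93 − 91 = 2, so about two thirds of the gain is lost.

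**Why the error falls below 5%.** The unadjusted test is kept only when the groups are close on the covariate. In those trials the group difference varies less than the unadjusted standard error assumes.

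**A second set-up.** One normally distributed covariate, adjusted for when its standardised difference exceeds 0.25, points the same way. At R² = 0.3, type I error is 3.3% and power at 10 points is 94.0% against 97.6%.

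**How often the judgement arises.** With 50 per group, one variable exceeds a standardised difference of 0.25 with probability 2(1 − Φ(0.25/0.2)) = 21%. The Assessment section lists nine items, counting fracture class. If they were independent, at least one would exceed it with probability 1 − 0.79⁹ = 88%.

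**The case against.** The strongest objection is that R² may be close to zero. The article ties displacement to nonunion, not to DASH. Suppose displacement acted only through nonunion, with an excess of 15 percentage points and an assumed penalty of 20 to 40 DASH points per nonunion. The mean difference would then be 0.15 × 20 = 3 to 0.15 × 40 = 6 points, and R² = (3/30)² = 0.01 to (6/30)² = 0.04. At those values the rule and prespecified adjustment hardly differ. This stands, and it is why the range has to start at zero. Displacement might affect function in other ways, but the article does not show it.

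A reader might infer that the rule inflates false positives or leaves the trial underpowered. Neither follows. With a fixed trigger the error is conservative, and simulated power at the design difference stays above 90%.

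A reader might also infer that the result can be steered. Blinding of the statisticians limits that. It does not prespecify the model.

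Finally, an analysis plan not shown might define the threshold. That would reduce discretion, but selection from observed imbalance would remain: the simulation already uses a fixed threshold.

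**Conclusion.** The point holds as one of prespecification and lost efficiency. That the model depends on the data follows from the wording and needs no assumption. The power given up at 10 points runs from nothing (R² up to about 0.02) to about 4.5 points (R² 0.3). At 7.5 points it reaches about 11 points.

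These figures rest on an assumed R², an assumed 50% displaced, one assumed trigger, and a single time point in place of the repeated-measures model.

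Three stronger readings are not supported:
- Displacement cannot be called the dominant predictor of DASH. It is a plausible one that the article does not document.
- No section shows age to be prognostic.
- A 10-point imbalance in displaced share has a 29% chance with 55 per arm, but that figure does not belong beside error rates computed with a 15-point trigger. At 15 points the chance is about 10% with 55 per arm and 13% with 50.

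The trial is not invalidated. This is an inexpensive improvement to the primary analysis that should be made.

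**What to change.** Before unblinding, and in a dated change, replace the conditional sentence with a short covariate set that enters the primary DASH model whatever the observed balance. It should contain at least displaced versus non-displaced, taken from the Edinburgh class. The article does not list that classification's categories, so state how they map to the two groups. Age may be added on clinical grounds. Report the unadjusted result, and any adjustment prompted by observed imbalance, as sensitivity analyses.

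No new data are needed. The cost is one or two degrees of freedom, and the gain is negligible if the covariate does not predict DASH. Even then the primary model is fixed in advance.

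### The additional DASH model that is meant to evaluate surgery contains no post-operative data, so its surgery term cannot estimate an effect of surgery

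*Protocol article*

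**What the plan says.** All of this stands in the Data analysis section of the protocol article unless another place is named.

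- **Intention to treat.** Patients who need additional interventions "will be followed up, and their results will be included in the group into which they had initially been randomised". Their DASH after surgery is therefore collected.
- **Main model.** "We will apply generalised mixed models in the intervention groups (two levels) and time-point assessments (seven levels) as fixed effects". The abstract adds patients as a random effect.
- **Additional model, aim.** "To evaluate the effect of surgical interventions required due to treatment failure in the DASH score a similar model will be adjusted including the effect". The added term is for surgery and has two levels.
- **Additional model, data rule.** The next sentence reads: "In this analysis, patients who are undergoing surgery will have the data analysed up to the last assessment before surgery".
- **Who is operated on.** The Secondary outcomes section defines treatment failure as "participants who will need (or are being considered for) a surgical intervention (e.g. symptomatic nonunion or malunion with intractable pain"). It expects symptomatic nonunion in 5% to 10% of participants, says these will be treated surgically, and applies a 6-month criterion for nonunion.

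No other section redefines the surgery term or restores the post-operative records to this model.

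**The concern.** The aim and the data rule are in consecutive sentences and cannot both be met. An effect of surgery on DASH can only be learned from DASH recorded after surgery, and the rule removes exactly those records. Whatever the surgery term then returns, it carries no information on surgery. Because failure is defined partly by symptoms, an ever/never coefficient could come out positive and be misread as surgery worsening function.

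There is a second, smaller issue. Surgery happens after randomisation and may follow from how the allocated device performed. Adjusting for it can take out the part of the bandage-sling difference that acts through failure, so the group coefficient of this model is not a clean randomised contrast.

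This is not a detail left to a later analysis plan. The protocol itself fixes both the term and the data rule.

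**Working it through.** The plan gives no numerical result for this model, so there is no figure to reproduce. The check is an identifiability argument, with a simulation as illustration.

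**1. How many patients carry the term.** From the expected 5% to 10% with symptomatic nonunion among 110 recruited: 0.05 × 110 = 5.5 and 0.10 × 110 = 11, so about 6 to 11. Surgery for other reasons would add to this.

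**2. The two possible codings, once post-operative rows are removed.**

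- *Time-varying (0 before surgery, 1 after).* Every row with value 1 has been deleted. The column is zero throughout and the coefficient is inestimable.
- *Ever/never, per patient.* Let e(k) be the mean DASH excess of later-operated patients at retained time point k, of K such points. With a random patient intercept and time as a factor, the coefficient estimates about Σe(k)/K. The true surgery effect enters only the deleted rows, so it does not appear in this expression.

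**3. Illustration.** Assumptions, none of them from the documents: 8 operated patients, surgery between the 6- and 12-month visits, a 20-point excess from 3 months, patient SD 10 and residual SD 11 (total √(100 + 121) = 14.9, close to the planned SD of 15), no device effect. There were 110 patients, seven time points and 40 simulated trials per scenario.

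| True surgery effect | Ever/never term, truncated data, no excess | Ever/never term, truncated data, 20-point excess | Full data, failure term plus time-varying surgery indicator |
|---|---|---|---|
| 0 | -0.22 | +6.45 | +0.65 |
| -10 | -0.22 | +6.45 | -9.35 |
| -20 | -0.22 | +6.45 | -19.35 |

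The SD across trials was 4.35 for the ever/never term and 4.27 for the surgery indicator. The formula in step 2 explains the third column. The excess is present at 2 of 6 retained time points, so 20 × 2/6 = 6.67, and -0.22 + 6.67 = 6.45. With only the six listed visits, and no baseline, it would be 20 × 2/5 = 8.0. The size depends on these inputs. The lack of any response to the true surgery effect does not.

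**4. Multiple imputation does not help.** In the data set for this model there is no observed post-operative value from which to impute one.

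**5. Size of the group-effect issue.** A second simulation with similar assumptions (60 trials per scenario) compared the group coefficient of the truncated surgery model with that of the intention-to-treat model. With equal failure rates they differed by about 0.02 points. With failure in 10% versus 5% they differed by about 0.3 to 0.4 points. Arithmetic agrees. If the devices differ only through failure, the intention-to-treat difference averaged over seven time points is 0.05 × (20 + 20 + 20)/7 = 0.43 with no surgery effect, and 0.05 × (20 + 20 + 5)/7 = 0.32 with an effect of -15. The surgery term absorbs most of this. The plan's minimal clinically important difference is 10 points.

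**The case against.** The strongest defence is that the authors meant a sensitivity analysis of bandage versus sling with the influence of surgery on DASH removed. Stopping at the pre-operative records is then deliberate and reasonable. This partly stands: the data rule suits that aim. But it is not the aim that the protocol states, it needs no surgery term, and the term would still not estimate an effect of surgery. The two sentences need reconciling on either reading.

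It is also fair that this is an ancillary model. The restriction is confined to it, while the intention-to-treat rule says of patients needing additional interventions that "their results will be included in the group into which they had initially been randomised". No primary or secondary outcome and no sample-size figure depends on the surgery model. That stands in full and limits the weight of the point.

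A reader might infer three stronger things that the documents do not support:

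- *That the surgery coefficient will have the wrong sign or a particular size.* Values such as +6.45 or +8.0 rest on an assumed 20-point excess and assumed timing. With no excess the mean was -0.22. A positive sign is plausible from the definition of failure, but it is not established.
- *That the randomised comparison is compromised.* The main model keeps operated patients, and the distortion in the extra model is small under the assumptions tested.
- *That a time-varying surgery indicator alone would repair the model.* It would not. In a six-visit simulation with the 20-point excess, with post-operative data kept, the indicator alone averaged +13.3, +3.3 and -6.7 for true effects of 0, -10 and -20, because it absorbs the failing patients' excess. With a failure term added, the means were -0.3, -10.3 and -20.3.

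**Conclusion.** The point holds for the additional surgery model and for nothing else. As written, that model cannot estimate an effect of surgery under either coding. This follows from the two sentences themselves and needs no numerical assumption. The term would rest on about 6 to 11 of 110 patients. The group coefficient of the model conditions on a post-randomisation event, but the expected distortion is small: about 0.4 points or less on average against a 10-point important difference, if failure is at most twice as common in one arm (10% versus 5%) and the excess is about 20 points from 3 months. The primary intention-to-treat mixed model is unaffected. Severity is moderate: a pre-specified analysis of the primary outcome cannot answer its stated question, but the trial's main conclusion does not depend on it.

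**What to change.** Keep the intention-to-treat analysis, with all post-surgery DASH, as primary. Then state which question the additional model answers and align its terms and data with it, before the statisticians are unblinded.

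1. **If the question is whether the bandage-sling comparison is sensitive to surgery:** drop the surgery term, set DASH after surgery to missing, handle it with the planned multiple imputation or the mixed model, and report only the group difference. The present data rule can stay; the sentence giving the aim changes. State the assumption that the missing values can be predicted from the earlier DASH scores and the other data in the model.
2. **If the question is the effect of surgery itself:** retain the post-operative assessments already collected. Include both a failure-status term, for the pre-surgery excess, and a time-varying surgery indicator. Say from which visit failure status counts. In the simulation that term began when the excess began; under the same assumptions, a term held constant over all visits would leave about 20 - 6.67 = 13.3 points in the surgery coefficient. Report the result as non-randomised and exploratory.

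The cost is a few lines of analysis wording and no new data. The downside of option 2 is imprecision: with 8 operated patients and the simulated SD of 4.27, a 95% interval is roughly ±1.96 × 4.27 = ±8.4 points, nearly the 10-point important difference.
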